### Sample size calculation

In our research protocol, we aim to assess the effectiveness of shockwave therapy on patients’ ability to engage in penetrative intercourse after a one-year period. Our initial observations revealed that 20% of patients achieved this without therapy, whereas an aim of 40% will achieve it with shockwave therapy. To design our study with statistical rigor, we utilized an allocation ratio of 2:1 (control:shockwave), and factored in a power of 80% and a significance level of 5%. Employing calculated Z-values for α and β, we derived an estimated sample size requirement of approximately 189 participants. The overall sample size was determined to be 189 patients, with 63 patients in the control group and 126 in the active treatment group.

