Accelerating cavernous nerve regeneration has shown potential in improving erectile function outcomes in animal models of radical prostatectomy. Although PDE5 inhibitors represent the first-line oral treatment for ED, their mechanism of action is dependent on the release of nitric oxide from functional CN innervated erectile tissue. Therefore, because of iatrogenic damage to the CN, the vast majority of patients undergoing RP are refractory to treatment of ED by PDE5 inhibitors (PDE5i). In the absence of effective oral treatments for ED, patients that undergo RP are recommended to undergo “penile rehabilitation”. This has a goal of maintaining the erectile tissue oxygenation levels in the acute phase of CN injury to prevent changes in penile architecture, until a time when there is functional CN repair. The strategy commonly utilizes (separately or in combination) intracavernosal injections, vacuum erection devices and low dose PDE5i administration.

The University of Miami “Erectile Preservation Protocol” is used for patients that will undergo a radical prostatectomy. This involves oral PDE5i which treat ED. Patients require additional treatment in order to obtain penetration in roughly 60%–75% of cases [5]. These more invasive treatments involve intracavernosal injections at the time of intercourse. The goal of the study is to have patients involved in penetrative intercourse as rapidly as possible without the use of more invasive treatment options.

The study is aimed at determining the safety and effectiveness of SWT in a patient population soon after? (Maybe even include the number of days to emphasize this is soon after RP) after radical prostatectomy. The rationale behind this is that SWT has been known to bolster angiogenesis and neurogenesis by increasing the levels of vascular endothelial growth factor. The shockwaves are focused onto linear segments that are aimed at the left and right corpora cavernosa and the crura. SWT has previously been shown to improve IIEF scores for organic erectile dysfunction [6]. However, there is a lack of sufficient data on the use of Li-ESWT for penile rehabilitation in the treatment of ED after prostate cancer therapy [7,8]. Existing protocols for SWT are not standardized and involve a limited number of participants with short follow-up periods. Our study aims to evaluate this question using a robust randomized protocol using an adequate number of participants and longitudinal follow up soon after RP.

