### Endpoints

The primary endpoint includes changes in the participant’s ability to have penetrative intercourse (without the use of intracavernosal injections, and with or without PDE5i use) from baseline to study completion. This information will be collected using the IIEF-EF questionnaire. The secondary endpoints are sexual activity improvement leading to optimal penetration at follow-ups which will be done according to: (i) Percentage of participants who achieve Minimal Clinically Important Differences (MCID) in IIEF score based on their ED severity at baseline. This is measured using the Change International Index of Erectile Function (IIEF-EF) Questionnaire score; (ii) Change in median International Index of Erectile Function–Erectile Function subdomain (IIEF-EF) from baseline to each follow-up time point in active therapy recipients compared to placebo; (iii) Change in median Sexual Encounter Profile questions number 2 and 3 from baseline to each follow-up time point in active therapy recipients compared to placebo; (iv) Change in median Global Assessment Questionnaire (GAQ) score from baseline to each follow-up time point in active therapy recipients compared to placebo; (v) Change in median Erection Hardness Scale (EHS) score from baseline to each follow-up time point in active therapy recipients compared to placebo; (vi) Changes in duplex ultrasound parameters from baseline to study completion in active therapy recipients compared to placebo.

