### Procedures involved

Upon evaluating the inclusion/exclusion criteria, patients will be recruited to the study and randomized into one of the two groups in a 2:1 ratio (randomization will be performed by a computer software maintained by the Desai Sethi Urology Institute). All participants will be instructed to follow the standard post-RP protocol for ED. Treatments will begin 6 weeks after the RP. The treatment sessions last approximately 20 minutes and are performed in an office environment (see below for session and treatment details). Participants randomized to the treatment group will receive one (1) shockwave session once per week for four (4) weeks, followed by one (1) shockwave session once per month (30 ± 7 days) for the next five (5) months. 1,440 shocks of treatment energy will be applied in every session to each treated region (left and right corpora cavernosa and crura) for a total of 12,960 shocks (Figure 1).

Participants randomized to the sham (control) group will have the same number of sessions, and the machine will be set to deliver 1,440 shock treatments, but a barrier will be placed around the shockwave probe to ensure that no shockwaves are delivered.

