### Data analysis

The average and standard deviation of all relevant variables, including demographic and baseline characteristics, primary and secondary outcomes will be calculated. IIEF-EF and EHS scores will be analyzed using ANOVA with repeated measures throughout the study, in order to compare the trends between the treatment and sham group. GAQ, SEP and success rates will be analyzed and compared between the groups according to Fisher’s exact test in each of the endpoints. The statistical significance will be set at P<0.05.

Demographic characteristics such as age and ED duration will be compared between treatment group and sham group using student’s T-Test. Other demographic characteristics, such as medical background and risk factors will be compared between these groups using Fisher’s Exact Test.

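### The 20% control rate behind the 189 patients is not reconciled with the protocol's own figure, which implies about 25–40% success on standard care, so the stated 80% power is not secured

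*Protocol article*

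**What the plan says.** Four statements in the protocol article bear on the control rate.

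- **Sample size calculation.** "Our initial observations revealed that 20% of patients achieved this without therapy, whereas an aim of 40% will achieve it with shockwave therapy". The outcome is penetrative intercourse at one year. With 80% power and 5% significance this leads to 63 control and 126 active patients.
- **Introduction.** The institution's erectile preservation protocol for prostatectomy patients is based on oral PDE5i. Of men managed this way the article says: "Patients require additional treatment in order to obtain penetration in roughly 60%–75% of cases". The next sentence identifies the extra treatment as injections at the time of intercourse.
- **Procedures involved.** "All participants will be instructed to follow the standard post-RP protocol for ED". This covers the sham arm as well as the active arm.
- **Endpoints.** The primary endpoint is the ability to have penetrative intercourse "without the use of intracavernosal injections, and with or without PDE5i use".

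Data analysis compares success rates between the groups with Fisher's exact test.

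**The concern.** Taken together, the Introduction, Procedures and Endpoints sections describe the sham arm: men on a PDE5i-based standard protocol, counted as successes if they penetrate without injections. The Introduction's figure for men who need more than that protocol has a complement, and the complement is the only other indication in the article of how this arm should perform. It is higher than 20% throughout, and the planned active rate equals its upper limit.

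The label attached to the 20% does not settle the matter, because it can be read in two ways. If it means no shockwave therapy, the 20% is meant as the sham-arm rate and lies below the range that the Introduction implies. If it means no treatment for erectile dysfunction at all, it describes men whom this trial does not contain. Under either reading the sample size section needs a control rate that it does not justify.

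At stake is how a non-significant result would be interpreted. If the control rate is higher than planned and the active rate stays near its target, the trial has little chance of showing a difference. If the gain over control stays near 20 points, little is lost. The article does not say which of these it is planning for.

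**Working it through.** **Inputs.** Control 20%, active 40%, power 80%, significance 5%, arms of 63 and 126 (Sample size calculation); Fisher's exact test for success rates (Data analysis); 60–75% needing additional treatment (Introduction). The article does not state whether the test is one- or two-sided. I take it as two-sided, which reproduces the stated total; a one-sided test would give 147. I treat success on the primary endpoint as a yes/no outcome at one year, as the sample size section does.

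**Step 1: reproduce 189.** Normal approximation with pooled variance under the null, no continuity correction, *k* = 2 active patients per control:

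n(control) = [1.960·√(p̄(1−p̄)(1+1/k)) + 0.8416·√(p₁(1−p₁)+p₂(1−p₂)/k)]² / (p₂−p₁)²

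With p₁ = 0.20, p₂ = 0.40 and p̄ = (0.20 + 2×0.40)/3 = 0.3333:

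- first term: 1.960 × 0.5774 = 1.1316
- second term: 0.8416 × 0.5292 = 0.4453
- n = (1.5769)² / 0.04 = 62.2, rounded up to 63

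So 63 + 126 = 189, an exact match. Power at 63/126 is 80.6% by this approximation and 78.8% for the two-sided Fisher test by exact enumeration.

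**Step 2: implied control rate.** 1 − 0.75 = 0.25 and 1 − 0.60 = 0.40, so roughly 25–40%.

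**Step 3: power at 63/126 over that range.** Fisher power is the sum, over all pairs of success counts, of the two binomial probabilities wherever the two-sided Fisher p-value is below 0.05. The last column is the total needed for 80% power by the Step 1 formula.

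| Control | Active | Assumption | Fisher power | Normal approx. | Total N for 80% |
|---|---|---|---|---|---|
| 20% | 40% | as planned | 78.8% | 80.6% | 189 |
| 25% | 40% | active rate held | 50.2% | 53.3% | 348 |
| 30% | 40% | active rate held | 23.5% | 26.4% | 810 |
| 35% | 40% | active rate held | 8.3% | 9.6% | 3321 |
| 40% | 40% | active rate held | no effect to detect | – | – |
| 25% | 45% | 20-point gain kept | 74.6% | 77.4% | 201 |
| 30% | 50% | 20-point gain kept | 73.4% | 75.4% | 213 |
| 35% | 55% | 20-point gain kept | 72.9% | 74.4% | 219 |
| 40% | 60% | 20-point gain kept | 72.6% | 74.2% | 219 |
| 25% | 50% | rate doubled | 91.1% | 92.4% | 132 |

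**Step 4: active rate needed for 80% Fisher power at 63/126.**

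| Control rate | Active rate needed | Difference |
|---|---|---|
| 20% | 40.3% | 20.3 points |
| 25% | 46.3% | 21.3 points |
| 30% | 51.6% | 21.6 points |
| 35% | 56.7% | 21.7 points |
| 40% | 61.8% | 21.8 points |

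**The case against.** The strongest reply is that the 25–40% is not printed anywhere. It is the complement of a range given only approximately, without a time point or a described case mix, and it rests on a cited source that is not at hand. The trial admits men after non-nerve-sparing surgery and with any grade or stage, so its case mix may differ. The 20% is presented as the team's own observation of this outcome at one year. Other text is compatible with a low rate: the Introduction says that most men are refractory to PDE5i after prostatectomy and that about 80% have some degree of erectile dysfunction. This stands as a reason not to put 25–40% in place of 20%. It does not remove the need to explain the gap, since neither of those statements gives a rate for the primary endpoint.

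A reader might infer that the 20% comes from the wrong comparator. The documents do not establish that. In a paragraph about shockwave therapy, the natural reading of the label may well be no shockwave therapy, which is the sham condition. What remains then is a mismatch with the Introduction, and at its nearest point the gap is only 20% against roughly 25%.

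A reader might also infer that 80% power cannot be reached with 189 patients. Step 4 shows otherwise: it needs a gain of 21.3 to 21.8 points, against 20.3 at the planned control rate. The low figures of 50%, 24% and 8% require the active rate to stay at 40% while the control rate rises. The article calls 40% an aim and does not say that it would stay fixed. A doubling of the rate would even raise power, to 91% at 25% against 50%, although the article states no relative effect.

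**Conclusion.** The concern holds as an unreconciled planning input, not as an error of calculation. The total of 189 is correct for 20% against 40%, but the article's own description of standard care points to a higher control rate in the arm that receives it.

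Across 25–40%, power is below 80% both for the stated target and for the stated difference. With the active rate at 40%, it is at most about 50% and falls away as the control rate rises. With a 20-point gain, it is 73–75%, which is 4 to 6 points below the 78.8% that the same test has under the planned rates.

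This rests on three assumptions: that the Introduction's figure applies at one year to men like those enrolled, that men who need no additional treatment do achieve penetration, and that all 189 patients contribute an outcome. The first two cannot be confirmed from the article, so the size of the loss is a range that depends on which target is meant.

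**What to change.** Rewrite the Sample size calculation paragraph as follows:

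1. Replace the 20% and its label with a sourced one-year success rate for the actual comparator: men on the standard post-prostatectomy protocol, PDE5i allowed, injections not counted as success.
2. Reconcile that rate with the 60–75% in the Introduction. If 20% is retained, say why it is lower, for example because of a different time point or case mix.
3. State whether the target is a 40% active rate or a 20-point gain over control.
4. Keep 189, and restate power and detectable difference for control rates of 20–40% under the planned Fisher test. The active rates needed for 80% power are about 40%, 46%, 52%, 57% and 62% at control rates of 20%, 25%, 30%, 35% and 40%.

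The cost is one paragraph and no additional patients. The change does not restore lost power; it states what 189 patients can detect. The downside is that the stated power becomes less favourable.

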### Participants

The inclusion criteria are as follows: (i) Be willing and able to provide informed consent; (ii) Be male; (iii) Be ≥ 40 and ≤ 75 years of age (inclusive); (iv) Undergo radical prostatectomy for prostate cancer (nerve sparing or non-nerve sparing without neoadjuvant chemotherapy or radiation therapy.); (v) Be at least six weeks post radical prostatectomy; (vi) Be in a stable sexual relationship for over 3 months prior to enrollment; (vii) Have a serum testosterone level of 300 ng/dL-1000 ng/dL within 1 month prior to enrollment; (viii) Have a HbA1c level ≤ 7% within 3 months prior to enrollment; and (ix) Have undetectable PSA value at the time of enrollment. Patients of all prostate cancer grades/stages and Gleason scores will be included as long as no adjuvant or salvage treatment is needed. Patient drop out will be due to patient preference, adverse effects, cancer recurrence, or need for further cancer treatment.

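### The 189 to be recruited equals the zero-drop-out Z-test requirement, so the stated 80% power does not survive the drop-out the plan expects

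*Protocol article*

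**What the plan says.** The Sample size calculation section of the protocol article starts from two rates: "20% of patients achieved this without therapy" and "an aim of 40% will achieve it with shockwave therapy". It then "factored in a power of 80% and a significance level of 5" per cent, uses Z-values, and reports about 189 participants, "with 63 patients in the control group and 126 in the active treatment group". No drop-out term appears. The Methods paragraph of the Abstract and the opening of Materials and Methods give the same 189 as the number to be recruited and randomised.

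The Participants section expects losses: "Patient drop out will be due to patient preference, adverse effects, cancer recurrence, or need for further cancer treatment". Materials and Methods puts total duration at 13 months, and Table 1 places the final questionnaires at Month 12.

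On the test, the Data analysis section says that GAQ, SEP and "success rates will be analyzed and compared between the groups according to" Fisher's exact test, and adds: "The statistical significance will be set at P<0.05".

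**The concern.** A sample size from a Z-value formula is the number of men who must be analysed. If the same number is recruited, the stated power holds only when every man supplies the primary outcome. The plan foresees that some will not, because of preference, adverse effects, recurrence or further cancer treatment, yet adds nothing for them. A non-significant result would then be read against 80% power that the design does not have.

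A smaller second point is that Fisher's exact test is conservative. If it is the test applied to the primary endpoint, power is a little below the Z-test figure even with complete data.

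**Working it through.** **Inputs.** Control rate p1 = 0.20, active rate p2 = 0.40, power 80%, alpha 5%, and 63 control with 126 active, all from the Sample size calculation section. Sidedness is not stated. Two-sided is assumed because it reproduces 189; the same formula one-sided gives 147.

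**Reproducing 189.** Pooled-variance formula with two active men per control:

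- Pooled rate = (0.20 + 2 × 0.40)/3 = 1/3.
- Null term: 1.960 × √[(1 + 1/2) × (1/3) × (2/3)] = 1.960 × 0.5774 = 1.1316.
- Alternative term: 0.8416 × √[0.20 × 0.80 + (0.40 × 0.60)/2] = 0.8416 × 0.5292 = 0.4453.
- Control n = (1.1316 + 0.4453)² / 0.20² = 62.2; active n = 124.3.
- Rounding control up to 63 and doubling gives 63 + 126 = 189, with zero drop-out.

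**Margin on the Z-test.** Power = Φ[(0.20 × √n − 1.1316)/0.5292], where n is the control arm:

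- n = 63: Φ(0.862) = 80.6%.
- n = 62 (62 + 124 = 186, three men lost, 1.6%): Φ(0.838) = 79.9%.

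**Fisher with complete data.** All outcomes of the two binomials were enumerated, rejecting when the two-sided Fisher p-value (probability ordering) is below 0.05. Power at 63/126 is 78.8%. It first reaches 80% at 66 + 132 = 198 (80.6%; 195 gives 79.8%), which is 9 men more than 189.

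**With drop-out.** The article gives no rate, so 5 to 20% is assumed, equal in both arms. In the last column all 189 are analysed with both rates multiplied by (1 − d), for example 18% against 36% at d = 10%. This treats 20% and 40% as rates among completers.

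| Assumed loss | Analysed, control/active | Z-test | Uncorrected chi-square, exact power | Fisher, drop-outs not analysed | Fisher, drop-outs as non-success |
|---|---|---|---|---|---|
| 0% | 63/126 | 80.6% | 81.1% | 78.8% | 78.8% |
| 5% | 60/120 | 78.5% | 79.2% | 77.9% | 76.1% |
| 10% | 57/113 | 76.2% | 76.7% | 74.2% | 72.9% |
| 15% | 54/107 | 73.7% | 74.5% | 70.5% | 69.1% |
| 20% | 50/101 | 70.5% | 71.7% | 69.3% | 64.7% |

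**Alternative tests with complete data.** Mid-p gives 82.2% and uncorrected chi-square 81.1%. At a common rate of 20%, true size is about 3.9% for Fisher, 4.9% for mid-p and 5.2% for chi-square.

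**The case against.** **The Fisher shortfall is trivial.** This stands. It is 1.2 points, or 9 men, against a figure that the article itself calls approximate. It would not be a finding alone and only adds to the drop-out problem.

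**The article does not name the primary test.** This also stands. The Endpoints section collects the primary outcome through the IIEF-EF, and Data analysis sends IIEF-EF scores to repeated-measures ANOVA and success rates to Fisher. Fisher is the likelier reading for a yes/no endpoint sized on two proportions. The drop-out point does not depend on it, because the Z-test column falls below 80% too.

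**The derivation may be a different one.** The section says "we utilized an allocation ratio of 2:1 (control:shockwave"), the reverse of its own arm sizes. With that ratio the unpooled formula gives 125.6 + 62.8 = 188.4, hence 126 + 63, which is again a zero-drop-out figure. With 126 control and 63 active, Fisher power is 79.3%. Alternatively, the unpooled formula with twice as many active men gives 165, and 189 would then hide an allowance of 1 − 165/189 = 12.7%. Nothing in the article suggests this, and exact power at 55/110 is only 75.4% (chi-square) or 73.3% (Fisher).

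**The size of the loss is assumed.** This stands, so only a range can be given. Entry requires undetectable PSA and no need for adjuvant or salvage treatment, which may keep losses down. If 20% and 40% already cover all randomised men, the non-success column double-counts.

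**Drop-outs may be handled elsewhere.** A reader might infer from the Participants section that men who drop out leave the randomised comparison. It lists reasons for dropping out and does not say that. Analysis population and missing-data rules may be in the statistical analysis plan, so no criticism of them is made here. Such rules would not add an allowance to a target sized without one.

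**Conclusion.** The point holds as a limited error in the stated power. The analysed and recruited numbers are both 189, there is no visible allowance for drop-out that the plan expects, and the margin is about three men. That conclusion needs no particular attrition rate, only the two-sided 5% level that reproduces 189.

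The size does depend on assumptions. At 10% loss, Fisher power is about 73 to 74%, a type II error of about 26 to 27% against the 20% implied. At 20% loss, power is about 65 to 69%.

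The point should be fixed, but it is not a fault that invalidates the trial: type I error and the randomised comparison are untouched. The documents do not support the stronger readings that Fisher's test alone undermines the design, or that drop-outs are excluded from analysis.

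**What to change.** In the Sample size calculation section, restate the power for the test actually planned and for an explicit attrition assumption, using the figure that matches how drop-outs will be handled. With Fisher's exact test and 10% loss, 189 men give about 74% power if drop-outs are not analysed, or about 73% if they are scored as non-success. The two figures should not be mixed.

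Optionally, name a mid-p or uncorrected chi-square test for the primary comparison. With complete data this recovers 3.5 points (82.2 − 78.8, before rounding) or 2.4 points (81.1 − 78.8, before rounding). For the chi-square test with drop-outs not analysed, the table shows about 1.3 to 4 points. The downside is that Fisher's strict guarantee on type I error is given up.

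The cost is one reworded passage and a less favourable stated power; no extra patients are required. If the sponsor would rather keep 80%, an assumed 10% loss with drop-outs not analysed implies 189/0.9 = 210 men on the Z-test basis, or 198/0.9 = 220 with Fisher.
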